#### Aim 2:

Estimate the cost of implementing and sustaining each intervention (Stepped Care with: a] *A.S.K.-PrEP* + CM; b] CM alone) and incorporate these costs into a comprehensive cost-effectiveness analysis to determine the value of each intervention relative to SOC, and to each other, from the healthcare-sector, state-policymaker, and societal perspectives.

#### Hypothesis 2

The Stepped Care approach with *A.S.K.-PrEP* + CM will be the most cost-effective intervention, despite its relatively high sustainment cost, due to its greater effectiveness resulting in larger improvements along the PrEP Care Continuum, and in SUD, thereby generating: (a) reduced utilization of high-cost healthcare, safety-net, and criminal-legal resources; and (b) increased productivity, time free from primary substance, and quality-adjusted life-years (QALYs). Stepped Care with CM alone will be the next best “value” for the same reasons.

#### Secondary Aim 1:

Estimate the individual effects of specific substances (e.g., methamphetamine vs. opioids), routes of administration (injection vs. non-injection), severity of SUD (mild, moderate, severe), social and structural determinants of health (e.g., poverty, housing insecurity, food scarcity, educational attainment, lack of insurance), and differing individual-level characteristics (e.g., sexual/gender identity, racial/ethnic identity, age) as moderators of outcomes among trans women and SMM with an SUD.

#### Exploratory Aim 1:

Evaluate intervention engagement (number of *A.S.K.-PrEP* navigation sessions in the initial 3-months) and intervention response (responders vs. non-responders) by chosen PrEP modality (i.e., oral daily [TDF/FTC or TAF/FTC] or long-acting injectable cabotegravir).

### Randomization ratio and power calculation

The 3:1 initial randomization ratio was selected as a means of increasing the likelihood that an adequate number of participants receive each of the two Stepped Care approaches. Because our second-stage randomization only occurs in non-responders, there is some uncertainty at baseline as to how many participants will ultimately be in each of the three arms. We used Monte Carlo simulations to establish under a range of scenarios that a sample size of *n* = 250 and the selected randomization ratios would ensure at least 80% power to detect a clinically meaningful difference of 20% or more in the proportion persistence/adherence under intervention vs. SOC.

### Community Advisory Board (CAB)

Two long-standing and ongoing CABs, one trans-specific and one SMM-specific, participate in all aspects of the study. The CAB members are requested to provide feedback on all stages of study development, implementation, recruitment strategies, interpretation of findings, and address any challenges encountered. Both CABs are multi-cultural and composed of individuals both living with and at risk for HIV, social service providers, community members, consumers, evaluation professionals, and influencers.

### Interventions

#### A.S.K.-PrEP intervention

*A.S.K.-PrEP* is a PrEP navigation intervention with SMS support. The navigation component is based on mechanisms of the Reasoned Action Approach [50], and the SMS support component is based on Social Support Theory [51]. The *A.S.K.-PrEP* intervention was adapted from Anti-Retroviral Treatment and Access to Services (ARTAS), the 5-session Centers for Disease Control and Prevention (CDC) evidence-based intervention, delivered over 3 months, for linking PWH into HIV care. Formative work was conducted to modify ARTAS to focus on linking high-risk, HIV-negative trans women and SMM into PrEP care [49]. In Session 1, the PrEP navigator uses the Needs and Barriers Assessment (NBA) to identify those pertaining to PrEP care, including substance use and behavioral health needs; adherence goal(s); and methods to achieve adherence. PrEP (TDF/FTC, TAF/FTC, Cabotegravir) and clinic options are discussed. In Sessions 2–5, PrEP navigators use the information from the NBA to help participants overcome barriers to PrEP adherence, and work with participants to address their SUD and need for additional auxiliary services.

A shorter version of the NBA (NBA-Lite) is administered at the beginning of Sessions 2–5 as a check-in and to assess progress through the PrEP Care Continuum; participant-centered treatment plans are reviewed and revised as needed. The participant-centered dialogical strategies are premised on Reasoned Action Approach: (1) identify barriers to PrEP, including substance use; (2) identify the participant’s readiness to address their SUD and link into other auxiliary needed services; and (3) increase the participants’ skills and self-efficacy in working with PrEP providers and other social service and treatment facilities. The PrEP navigator will link participants into SUD treatment and other ancillary behavioral health and support services, according to their unique barriers, with the ultimate goal of PrEP initiation, adherence, and persistence; services may include mental healthcare, counseling for intimate partner violence, food insecurity, housing instability, hormone therapy, among others. Discussions of PrEP adherence, reductions in substance use, substance use treatment, and other behavioral health concerns are discussed throughout the 5 sessions (see Fig. 2). All PrEP navigators are all peers, with past lived experiences directly related to the participants.

**Fig. 2 Fig2:**
[figure not shown]
PrEP Navigation Delivery System

#### SMS support

One PrEP social support text message (see Table 1) is transmitted weekly; participants may choose to have the text messages delivered via cell phone or email. The automated text message delivery system is developed in and delivered by TextMagic on a pre-programmed schedule. To maintain interest and enthusiasm for the intervention, participants receive 12 trans- or 12 SMM-specific messages during the 3-month intervention period. Participants that continue with the A.S.K.-PrEP intervention for an additional 3 months receive the same SMS support intervention. Participants are asked to notify a research assistant immediately if they lose their cell phone or changed their phone number.

**Table 1 Tab1:** Sample text messages for PrEP adherence geared towards trans women and SMM

Trans Women-specific Text Messages	SMM-specific Text Messages
“Hormones are safe to take with PrEP! PrEP is safe to take with hormones! You can do both!”	“If you can see your friends, you can get your PrEP”
“Hey gurl, you can prioritize PrEP, even if you’re high.”	“You can prioritize PrEP, even if you’re high”
“You can take care of yourself and your trans community by taking PrEP.”	“Take care of yourself, take care of your sex partners, take PrEP.”

#### Contingency management (CM)

CM is a behavioral economics intervention that posits the application of contingencies to motivate individuals toward health-promoting behavior change [52, 53]. Behavioral economics incorporates direct and immediate reinforcement – the primary construct in the operant form of learning theory – whereby behaviors are learned through rewards. CM uses an operant reinforcement schedule that provides increasingly valuable rewards for consecutive urine samples that are nonreactive to the participant’s targeted SUD. As successive nonreactive urine samples are achieved and voucher points increase, so does one’s sense of self-efficacy to continue providing nonreactive urine samples.

At the 3-month follow-up assessment, non-responders (see Table 2) are stepped and re-randomized to CM, either in concert with *A.S.K.-PrEP* or alone. At the first CM session, a research assistant provides a 15-minute orientation to the CM procedures, which includes an explanation of the progressive, voucher-based reinforcement schedule. Thereafter, participants will meet with a research assistant thrice weekly to provide a urine sample. The CM protocol can be simplified into these guidelines: (1) participants receive a $2.50 voucher for the first nonreactive urine sample for their targeted SUD; (2) participants receive a voucher reflecting an incremental increase of $0.50 for each subsequent nonreactive urine sample; (3) participants receive a bonus of $7.50 for each 3 consecutive nonreactive urine samples; (4) vouchers are redeemable at any time for goods or services, selected by the participant, that support a healthy and pro-social lifestyle, such as groceries, camera equipment, clothing, bicycle; (5) participants who produce a urine sample that is reactive to their targeted SUD, or who fail to submit a urine sample, do not receive a voucher for that particular CM visit and their subsequent voucher value is reduced to the initial $2.50; and (6) a rapid reset procedure allows participants to return to their place in the escalating CM schedule after producing 3 consecutive nonreactive urine samples. Participants who complete the CM intervention without a reactive urine sample earn $495 in vouchers (see Table 3). If a participant is diagnosed with a SUD for two or more substances, they are asked, “Which drug do you use most despite negative consequences?” and that drug is targeted in the CM intervention.

**Table 2 Tab2:** Step criteria at 3-month follow-up

**Step Criteria Based on PrEP:**
Has not initiated PrEP (either Truvada, Descovy or Cabotegravir)
On oral-daily PrEP but self-reports non-adherence (missed 4 or more days in a row) in past 3 months
On long-acting injectable but has not received 2nd dose within +/- 7 days of 28 days (i.e., 35 days) after 1st dose (only check this if 3-month follow-up takes place 35 days or more after 1st dose)

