**Step Criteria Based on Substance Use**:
Self-reported drug use of the targeted SUD diagnosed at baseline for 1 (or more) day(s) in the past 14 days
Positive urine drug screen for targeted SUD diagnosed at baseline

**Table 3 Tab3:** Contingency management (CM) Voucher-based escalating reinforcement schedule

Week #	Mon	Wed	Fri	Bonus	Weekly Totals	Total Earned
**Week 1**	$2.50	$3.00	$3.50	$7.50	$16.50	$16.50
**Week 2**	$4.00	$4.50	$5.00	$7.50	$21.00	$37.50
**Week 3**	$5.50	$6.00	$6.50	$7.50	$25.50	$63.00
**Week 4**	$7.00	$7.50	$8.00	$7.50	$30.00	$93.00
**Week 5**	$8.50	$9.00	$9.50	$7.50	$34.50	$127.50
**Week 6**	$10.00	$10.50	$11.00	$7.50	$39.00	$166.50
**Week 7**	$11.50	$12.00	$12.50	$7.50	$43.50	$210.00
**Week 8**	$13.00	$13.50	$14.00	$7.50	$48.00	$258.00
**Week 9**	$14.50	$15.00	$15.50	$7.50	$52.50	$310.50
**Week 10**	$16.00	$16.50	$17.00	$7.50	$57.00	$367.50
**Week 11**	$17.50	$18.00	$18.50	$7.50	$61.50	$429.00
**Week 12**	$19.00	$19.50	$20.00	$7.50	$66.00	$495.00
**Maximum CM Payout**:						$495.00

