For each effectiveness measure, we determine which intervention is most cost-effective using the rules of strong and extended dominance. Finally, we estimate acceptability curves for each ICER, which illustrate the probability that an intervention is cost-effective for different value thresholds [77].

*Secondary Aim. Determine individual effects of specific substances, routes of administration, severity of SUD, social and structural determinants of health, and differing individual-level characteristics as moderators of outcomes.* As with Specific Aim 1, we utilize LTMLE to estimate subgroup-specific treatment effects based on participant-level characteristics. The magnitude of intervention effects are compared across relevant subgroups to infer moderation of intervention outcomes. We use Benjamini-Hochberg corrections to account for multiple testing and control for the false discovery rate of moderators.

*Exploratory Aim: Evaluate intervention engagement (i.e., number of A.S.K.-PrEP sessions in the initial 3-months) and intervention response (responders vs. non-responders) by chosen PrEP modality (i.e., oral daily or long-acting injectable).* We compare unadjusted response rates between, and average levels of engagement across the PrEP modalities using descriptive statistics. We also present covariate-adjusted analyses that account for participant-level differences. Because this analysis involves self-selected medication adherence, we control for potential confounders of PrEP modality and response. We use the theory of directed acyclic graphs to determine an appropriate set of confounders, and TMLE to estimate the impact of the PrEP modalities on response. We use controlled direct effects to quantify the impact of intervention engagement as a mediator of intervention response and determine whether there is a differential impact of PrEP modality on response after controlling for engagement [78]. Causal sensitivity analyses are used to examine the robustness of our findings to the assumption of no unmeasured confounding.

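### Exploratory Aim 1 estimates the effect of PrEP modality on 3-month response, but the PrEP part of response is scored by different rules for oral and injectable users

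*Protocol article*

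**What the plan says.** Under Contingency management (CM), the protocol article ties response at 3 months to Table 2: "non-responders (see Table 2) are stepped and re-randomized to CM".

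The PrEP block of Table 2 has three lines. The first is failure to start PrEP. The second applies to oral users: "On oral-daily PrEP but self-reports non-adherence (missed 4 or more days in a row) in past 3 months". The third applies to injectable users and asks whether the second dose was received within 7 days either side of day 28 after the first. It carries a condition: "only check this if 3-month follow-up takes place 35 days or more after 1st dose".

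The substance-use block does not mention modality. It consists of a urine screen positive for the targeted substance and this line: "Self-reported drug use of the targeted SUD diagnosed at baseline for 1 (or more) day(s) in the past 14 days".

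Exploratory Aim 1 takes as an outcome "intervention response (responders vs. non-responders) by chosen PrEP modality". For it, the Statistical analysis/outcomes section compares unadjusted response rates and then uses "TMLE to estimate the impact of the PrEP modalities on response". It adds a mediation analysis: "We use controlled direct effects to quantify the impact of intervention engagement as a mediator of intervention response". Confounders are to be chosen with directed acyclic graphs. The stated robustness check is this: "Causal sensitivity analyses are used to examine the robustness of our findings to the assumption of no unmeasured confounding".

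**The concern.** The exposure in this analysis is oral versus injectable PrEP. The outcome is a label whose PrEP part is scored differently at each level of that exposure. Two groups with the same engagement could therefore show different response rates because of the rule alone.

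The planned safeguards deal with who chooses which modality. They do not deal with an outcome whose definition changes with the exposure, so the problem would remain even with no confounding at all. The controlled direct effect uses the same label and inherits the problem.

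At stake is the reading of one exploratory result. An estimate labelled as the impact of modality on response could be taken as evidence that one form of PrEP is better adhered to.

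**Working it through.** **1. The Table 2 rules side by side**

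| | Oral user | Injectable user |
|---|---|---|
| Failing event | self-reported run of 4 or more missed days | second dose not received on time |
| Window | past 3 months | one due date, days 21 to 35 after the first dose |
| Recent starters | scored | not scored if the first dose was under 35 days ago |
| Substance-use lines | same | same |

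**2. Injectable users under 35 days.** They have started PrEP, so the first line does not apply. They are not on oral PrEP, so the second does not apply. The third is not checked. They pass the PrEP block whatever they do. An oral user who started on the same day can fail.

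**3. Size.** The plan gives no figure for this aim, so there is none to reproduce. What follows is illustration only and rests on assumed rates.

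Assumptions:
- Both modalities have the same lapse rate, L = 0.2 per 30 days.
- First doses are spread evenly over the 91 days before the visit.
- An injectable user fails if a lapse falls in an at-risk window of w days.

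Formulas, with t the days since first dose:
- Oral failure: 1 − exp(−L·t/30), averaged over t from 0 to 91.
- Injectable failure: 1 − exp(−L·w/30) if t ≥ 35, otherwise 0. The scored share is 56/91 = 0.615.

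Results:
- Oral: 91 × 0.2/30 = 0.607, and 1 − (1 − exp(−0.607))/0.607 = 25.0%.
- Injectable, w = 14 (days 21 to 35): 0.089 × 0.615 = 5.5%. Gap 19.5 points.
- Injectable, w = 35 (all days from the first dose to the end of the window): 0.208 × 0.615 = 12.8%. Gap 12.2 points.

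The gap moves from 19.5 to 12.2 points on the choice of w alone, and the documents do not settle that choice.

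**4. Removing only the exemption.** Among users with 35 or more days on PrEP, oral failure is 33.9%. Injectable failure is 8.9% (w = 14) or 20.8% (w = 35), giving gaps of 25.0 or 13.1 points. Restricting to 35 days removes the free pass but not the difference in event and window.

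**5. Direction.** Suppose instead that 10% of oral users report a 4-day run and 30% of second injections are late. Then 0.10 − 0.30 × 0.615 = −0.085, a gap of 8.5 points against injectables. Separately, if oral users miss 10% or 20% of days independently, 99% or 89% have no 4-day run in 90 days. The rule could therefore favour either modality.

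**6. Dilution in the combined label.** The article does not say whether one failed block or both make a non-responder. Let a share s fail the substance-use block, equal by modality and independent of the PrEP block. A PrEP-line gap g becomes g(1 − s) if either block suffices and g·s if both are needed. For g = 19.5 points and s = 20%, 50% and 80%, the combined gap is 15.6, 9.8 and 3.9 points, or the same figures in reverse order.

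None of these figures covers people who had started PrEP before enrolment, whom the inclusion criteria admit.

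**The case against.** Much of the asymmetry comes from the dosing schedule. A daily pill and an injection share no adherence event. The second dose is due at day 28 and later injections follow at 2-month intervals (Dried blood spot section), so a third falls at about day 88 (28 + 60). For most people who start after enrolment, the second dose is the only one that can be scored by 3 months. Before day 35 its window is still open and nothing is overdue. This stands, and it is why Table 2 is reasonable for deciding who is stepped. It does not justify counting someone not yet assessable as a pass in a comparison between modalities.

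The estimand also has a legitimate reading: the effect of modality on meeting the programme's own step rule, and so on needing CM. Facing one dose instead of many pill-days is then part of the effect. This stands too, provided the result is described that way and not as an effect on a common adherence behaviour.

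The equal-lapse illustration charges oral users for days on which injectable users have nothing to miss. That is fair, and the figures should not be used as an estimate of the bias.

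Moving the causal analysis wholly to substance use would change the aim's question. That is why the substance-use analysis should be an addition, not a replacement.

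Finally, component reporting is often left to an analysis plan. However, the article itself states the outcome, the exposure and the estimator, and the point concerns how those three fit together.

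**Conclusion.** The point holds as a minor one. A modality contrast on the Table 2 label mixes any real difference in response with modality-specific scoring, and the stated safeguards do not separate the two. This follows from the text alone and needs no assumed rate.

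The size and the direction do not follow from the text. They depend on when people start, how often they lapse, how many fail the substance-use lines and how the two blocks combine. Only for injectable users under 35 days is the direction on the PrEP line certain: there the rule can only favour injectables.

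A reader might infer two stronger things:
- **That the plan favours injectables by a stated number of points.** The documents do not support this. The illustrative gaps rest on an assumed null, and plausible inputs reverse the sign.
- **That the main trial result is affected.** It is not. The primary contrast is Stepped Care against standard of care, and re-randomisation only needs a rule for who is stepped. Table 2 can serve that purpose as written.

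**What to change.** Change Exploratory Aim 1 only, and leave Table 2 as the stepping rule:

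- (a) Report the PrEP and substance-use components of response separately by modality.
- (b) Beside the planned combined-label analysis, add the TMLE and the controlled direct effect for the substance-use component, which is scored identically for both modalities.
- (c) Do not count injectable users under 35 days from first dose as passing the PrEP line. Show them as not yet assessable, and repeat the combined-label analysis among users of either modality with at least 35 days on PrEP. Note that this removes the exemption but not the difference in event and window.
- (d) Interpret the combined-label contrast as an effect on meeting the programme's step rule, not on a common adherence behaviour.

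The cost is a text change to one exploratory analysis. Each Table 2 line already has to be assessed for stepping, so no new data are needed and enrolment and stepping do not change. The downsides are a smaller sample in the restricted analysis and a narrower causal claim. In the substance-use analysis, anyone who started PrEP within 14 days of the visit has part of the 14-day recall window before the first dose, in both modalities alike.

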**Step Criteria Based on Substance Use**:
Self-reported drug use of the targeted SUD diagnosed at baseline for 1 (or more) day(s) in the past 14 days
Positive urine drug screen for targeted SUD diagnosed at baseline

**Table 3 Tab3:** Contingency management (CM) Voucher-based escalating reinforcement schedule

Week #	Mon	Wed	Fri	Bonus	Weekly Totals	Total Earned
**Week 1**	$2.50	$3.00	$3.50	$7.50	$16.50	$16.50
**Week 2**	$4.00	$4.50	$5.00	$7.50	$21.00	$37.50
**Week 3**	$5.50	$6.00	$6.50	$7.50	$25.50	$63.00
**Week 4**	$7.00	$7.50	$8.00	$7.50	$30.00	$93.00
**Week 5**	$8.50	$9.00	$9.50	$7.50	$34.50	$127.50
**Week 6**	$10.00	$10.50	$11.00	$7.50	$39.00	$166.50
**Week 7**	$11.50	$12.00	$12.50	$7.50	$43.50	$210.00
**Week 8**	$13.00	$13.50	$14.00	$7.50	$48.00	$258.00
**Week 9**	$14.50	$15.00	$15.50	$7.50	$52.50	$310.50
**Week 10**	$16.00	$16.50	$17.00	$7.50	$57.00	$367.50
**Week 11**	$17.50	$18.00	$18.50	$7.50	$61.50	$429.00
**Week 12**	$19.00	$19.50	$20.00	$7.50	$66.00	$495.00
**Maximum CM Payout**:						$495.00

#### A.S.K.-PrEP + contingency management

Participants stepped and randomized into *A.S.K.-PrEP* + CM receive the same *A.S.K.-PrEP* and CM interventions (described above), but in concert to increase intensity and simultaneously address SUD, and PrEP initiation, adherence, and persistence.

#### Standard of care arm

The SOC arm provides PrEP education, information, and referrals. Those randomized to the SOC arm at baseline receive a 20- to 30-minute educational session on PrEP; the CDC “PrEP 101” and “PrEP Medication Guide” pamphlets [54, 55]; and a list of clinics that provide PrEP in LAC. For those randomized into the SOC arm, the same educational session is repeated following the 3-month follow-up assessment visit. A research assistant provides the PrEP education, information and referrals at baseline and the 3-month follow-up assessment visit.

### Sample

The inclusion criteria for participation are: (1) self-identified trans woman or SMM (including trans man/trans masculine male who have sex with men); (2) age 18 years or older; (3) verified HIV negative; (4) identified as “high risk” for HIV based on the Los Angeles County (LAC) criteria of: (a) sex without a condom, (b) methamphetamine use, (c) sex with an HIV-positive partner, or (d) injection drug use [56]; 5) SUD (injection and non-injection) verified by the Diagnostic and Statistical Manual of Mental Disorders, Fifth Edition (DSM-5) (excluding cannabis use disorder alone, as current research has demonstrated that cannabis use only is not an HIV risk) [57]; 6) willing to provide informed consent; and 7) willing to comply with study requirements. Additional inclusion criteria for those who previously initiated PrEP are: missed 4 or more doses of oral-daily PrEP during any week in the previous 30 days, and/or no PrEP care visits in the past 3 months. Individuals that do not meet all criteria or are unable to pass an informed consent quiz are excluded. Should a participant be identified as having kidney or liver dysfunction sufficient to contraindicate PrEP use (creatinine clearance < 60 mL/min), that individual is withdrawn from study participation, but may re-screen for eligibility once adequate renal and/or liver function has been established and medically documented (≥ 60 mL/min).

